### Intervention

We have developed an intervention through a process of identifying inappropriate prescriptions of antibiotics for RTIs; either as particular drugs, or drugs linked to specific diagnosis. Identification of irrational antibiotic treatment is based on guidelines on antibiotic prescriptions issued by The Norwegian Board of Health 2000 [35]. This guideline was distributed to all Norwegian GPs in 2000 and is also available on the Internet. Examples of suboptimal antibiotic prescribing according to this guideline are listed in Table 1.

In order to implement a more rational prescribing, 13 GPs will be recruited as tutors, each with responsibility for the intervention in three peer CME groups. Each tutor, named Prescription Peer Academic Detailer (Rx-PAD), will receive a four days' pre-study training program, focusing on the evidence of antibiotic treatment of RTI, pedagogical intervention techniques, and how to install and use the data-software program for data collection. When recruiting Rx-PADs, emphasis is also laid on the economic independence from any pharmaceutical manufacturers.

The tailored intervention towards the GPs in the peer groups will include two educational outreach visits, both performed by the same Rx-PAD. The elements of the intervention are discussions within the peer group, collection of individual prescription data, audit based on individual feedback reports, as well as a one day regional work-shop, see Figure 1.

In the first outreach visit, the main elements of the intervention will be presented, with special emphasis on evidence-based prescription of antibiotics for RTIs in out-patients, choice of first-line drugs, and treatment goals. During the visit, a software package will be delivered to each participant, for installation on own practice computer with EPR. This enables the participants to extract individual data from the preceding 12-month period. These data will be used for feedback reports and comprise the baseline data used in this study. For two of the four EPR systems (WinMed^® ^and ProfDoc Vision^®^), the software package will also include computerized "pop-ups" on the computer screen when antibiotics are prescribed, in order to mark prescriptions as either "regular" (to be dispensed immediately) or "delayed" (to be dispensed in n days) (Figure 2). Data from these "pop-ups" will be integrated in the second data extraction, and will represent a separate factor in the subsequent data analyses. These two EPR systems are probably used by more than half of all GPs involved in this study. Prescription data will be collected on diskettes and analyzed by research staff, followed by an individual prescription report, which will be mailed to each participant.

The second outreach visit, which will take place within two months after the first visit, focus on the newly revealed prescription patterns. Rx-PADs will facilitate the discussion within the peer groups, based on individual feedback reports, enabling participants to compare own prescription patterns with overall averages. This will trigger discussion within the peer group, aimed at critical reflection towards own prescription strategies for RTIs and the disclosure of areas where individual improvements are desirable and possible.

About three months after the second outreach visit, all participants will be gathered in regional work-shops where evidence-based rationale behind pharmacological treatment of RTIs in out-patients will be outlined in more depth on the basis of baseline prescription data. Twelve months after the first data extraction, a second data extraction of the GPs' prescribings for the preceding 12-months period will be undertaken and new individual reports will be sent to the participants.

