### Objectives

The primary objective of this trial is to evaluate the effects of a tailored intervention towards Norwegian GPs for a more rational approach to antibiotic prescriptions for RTIs. Our hypothesis is that an educational intervention program carried out during a 6-month period will be effective in improving prescribing patterns by reducing the total number of antibiotic prescriptions, as well as reducing the relative amount of broad-spectrum antibiotics, with special emphasis on macrolides. Degree of improvement will be measured by prevalence of specific antibiotic prescriptions and the combination of particular antibiotic prescriptions and selected diagnostic codes, according to the International Classification of Primary Care (ICPC-2) [76]. Secondary objectives are to estimate the agreement between prescribed and actually dispensed drugs, the latter based on dispensed drugs recorded in the Norwegian Prescription Database (NorPD), a national registry including data for all prescription drugs issued at Norwegian pharmacies, established in 2004 [77]. We will also explore effect of "delayed prescriptions" on the antibiotic prescription patterns.

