### Outcome measures

Primary outcome measures will be changes in prescription patterns after the tailored educational intervention in terms of prescriptions for antibiotics in out-patients with RTIs. The intervention will include the option of "delayed prescriptions". Following the intervention, prescription data will be collected one year after the first (baseline) gathering of prescription data. Change in prescription patterns in the intervention group will be compared with the non-intervention control group, and with a sample of Norwegian GPs not included in the current trial. The latter data will be provided by the NorPD. Outcome measures are summarized in Table 2.

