## Discussion

A thorough evaluation of the diagnostic indications for antibiotic treatment of RTIs may impose important benefits, whereas inappropriate prescribing may lead to undesirable consequences like the development of antibiotic resistance. We have therefore developed an intervention aimed at supporting the implementation of more rational antibiotic prescribing patterns for RTIs in GP settings and planned a trial to assess the effectiveness of this intervention.

The control group in this study will not receive any intervention towards prescriptions of antibiotics, but will be assigned to another drug prescription trial, where they will recieve an educational intervention for improving their prescribing (other than antibiotics) for elderly outpatients ≥ 70 years [83]. As such, the control group may be susceptible to changes in their general prescription patterns, i.e. a possible Hawthorne effect. To control for this, we will be able to analyze prescription patterns for *all *Norwegian GPs not included in the current trial, using data from the NorPD [77]. These data, however, will not be linked to diagnoses, and the comparison will therefore be performed on total prescription of the different antibiotics, except those exclusively used for urinary tract infections.

To assure a highest possible response rate from the participating GPs, we will provide technical telephone support during the data collection period. Furthermore, the participants must provide data to receive an individual feedback report. Also, the Rx-PAD will remind their group participants to send in data sets before the second peer group meeting.

Because the aim of this study is to improve quality according to good clinical practice, the study is not likely to imply risks or impaired quality of care for the patients involved. The risk of data-misuse is limited due the fact that the research database will only be linked to de-identified patient ID numbers.

The estimated ICC-value, which will be used in the statistical analyses, reflects the three different levels of clustering; each participating doctor, each clinic, and each peer CME group. Our ability to establish an exact ICC-value is limited, due to few comparable studies.

A reduction of inappropriate prescriptions by one third compared to the baseline figures may seem too optimistic. However, in the light of a previous study [62], we still believe that this is a realistic goal.

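### Both 12-month windows are split at the first data extraction, so early post-visit weeks can enter the baseline, and 3 to 5 delivery months fall in the follow-up year that is planned on an 18% post-intervention level

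*Protocol article*

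**What the plan says.** All references are to the protocol article.

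- **First extraction.** At the first visit, where the prescribing evidence is presented, the Intervention section provides: "During the visit, a software package will be delivered to each participant, for installation on own practice computer with EPR". It continues: "This enables the participants to extract individual data from the preceding 12-month period". These data are the study baseline.
- **Latest date for it.** According to the Discussion, "the Rx-PAD will remind their group participants to send in data sets before the second peer group meeting". The Intervention section places that second visit as one "which will take place within two months after the first visit".
- **Rest of delivery.** The second visit uses feedback reports built from the first extraction. Then: "About three months after the second outreach visit, all participants will be gathered in regional work-shops". The Objectives describe "an educational intervention program carried out during a 6-month period".
- **Second extraction.** "Twelve months after the first data extraction, a second data extraction of the GPs' prescribings for the preceding 12-months period will be undertaken".
- **Outcome and target.** Outcome measures defines the primary outcome as change in prescribing after the intervention and adds: "Following the intervention, prescription data will be collected one year after the first (baseline) gathering of prescription data". Sample size and statistics powers on a fall from 27% to an 18% level described as post-intervention, but counts 300 cases per GP over the intervention period. The Abstract and the opening of Methods/Design measure one year after initiation.
- **Analysis.** Sample size and statistics plans post-test comparisons between arms, with analysis of covariance as an option.

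**The concern.** The date that separates the two years is an administrative event inside the delivery period. This has two consequences.

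First, prescribing between the first visit and the extraction counts as baseline in the intervention arm although those GPs have already heard the recommendations. Control groups get no antibiotic programme, so the shift is one-sided and makes a measured change too small.

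Second, the follow-up year opens before any GP has seen a feedback report. It averages partly treated and fully treated months, whereas the 18% target is worded as a level reached after the intervention. If 9 points is the effect of the completed programme, the measured contrast is smaller than the one the trial was sized for. If 9 points is the average over the first year, there is no mismatch. The text does not say which.

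**Working it through.** **1. The plan's own figure.** Inflation factor: 1 + (2100 − 1) × 0.085 = 179.4 (stated as 179). For 27% against 18%, two-sided 5%, 80% power, with continuity correction: 359 per arm before inflation. 359 × 179 / 2100 = 30.6, so 31 groups per arm, as stated. (Without the correction: 337, or 28.7 groups. The article states neither sidedness nor correction; this combination reproduces 31.)

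**2. Timeline, in months from the first visit.** Extraction at L. Second visit at 2 at the latest, workshop about 3 later, so at 5 at the latest. Extraction cannot precede the first visit. It must also leave time before the second visit for posting, analysis and return of reports, so 0 ≤ L < 2.

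- Baseline runs from L − 12 to L: treated months in it = L.
- Follow-up runs from L to L + 12: overlap with delivery = 5 − L, that is 5 of 12 months at L = 0, 4 at L = 1, just over 3 as L nears 2.

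The report, second visit and workshop depend on or follow the first extraction, so they fall in the follow-up year whatever L is.

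**3. Leakage.** Largest when the full 9 points starts at the first visit and L nears 2: 9 × 2/12 = 1.5 points, a bound that is not reached. The change contrast then goes from 9.0 towards 7.5, while the post-test contrast stays at 9.0.

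**4. Overlap.** The document gives no onset shape, so these are assumptions. At L = 0 the year-average effect is:

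- immediate: 9.0 points
- none until the second visit: 9 × 10/12 = 7.5
- linear over 5 months: (4.5 × 5 + 9 × 7)/12 = 7.1
- none until the workshop: 9 × 7/12 = 5.25

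**5. Power.** Effective n per arm = K × 2100/179: 363.7 for K = 31, and 469.3 for K = 40 (half of the 80 groups sought). Power = Φ[(d − 1.96·SE0)/SE1], with SE0 = √(2p̄(1 − p̄)/n) and SE1 = √((p1q1 + p2q2)/n), p1 = 0.27, p2 = 0.27 − d, no continuity correction (hence 83% rather than 80% at 31).

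| Onset | L | Average effect (points) | Power, 31 per arm | Power, 40 per arm |
|---|---|---|---|---|
| Immediate | 0 | 9.0 | 83% | 91% |
| None until second visit | 0 | 7.5 | 67% | 78% |
| Linear over 5 months | 0 | 7.1 | 62% | 73% |
| None until workshop | 0 | 5.25 | 38% | 47% |
| Linear over 5 months | 2 (limit) | 8.3 | 76% | 86% |
| None until workshop | 2 (limit) | 6.75 | 57% | 68% |

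**6. Precision of a post-workshop analysis.** Seven months give about 2100 × 7/12 = 1225 cases per group. Groups needed for 9 points: 359 × (1 + 1224 × 0.085)/1225 = 30.8, against 359 × 179.4/2100 = 30.7 for the full year. The intra-cluster correlation dominates, so the shorter window loses almost nothing, provided that correlation is unchanged.

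**The case against.** The measured quantity has support in the text. The Abstract and Methods/Design refer to one year from initiation, and the sample size counts cases during the intervention period. The first-year effect of a programme is a legitimate pragmatic target, and two full years balance season, which matters because the Background acknowledges winter peaks. The statement "Following the intervention, prescription data will be collected one year after the first (baseline) gathering of prescription data" is literally true, since collection at month 12 does follow delivery. The first visit already conveys the evidence and drug choices, so a zero effect until the workshop is the least plausible shape. The baseline anchor is inferred: the preceding 12 months could mean those before the visit. The article is condensed, and its timeline figures and outcome table are not visible.

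Most of this stands, and it rules out several stronger readings that a reader might infer:

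- *The baseline absorbs two treated months while the follow-up year also holds the whole delivery period.* Each week of lag moves one week from one window to the other; both maxima cannot occur together.
- *The 5.25-point average and the 1.5-point leakage add up.* They need opposite onset assumptions. If nothing happens before the workshop, leakage is zero.
- *The planned primary test is biased by the baseline.* A post-test comparison does not use the baseline.
- *The post-workshop window should be primary.* That would replace the estimand and give up season balance, which is a trade-off and not the correction of an error.

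What the objection does not remove is that Outcome measures and the 18% target are worded as post-intervention while other sections point to the first year, and that the change outcome rests on a baseline that may end after treatment has begun.

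**Conclusion.** The point holds in limited form. On the natural reading, the two years split at the first extraction. The baseline of the intervention arm can take in up to just under two treated months, and the follow-up year overlaps delivery by roughly 3 to 5 of 12 months. The second figure uses the upper end of the visit schedule; the Objectives give six months for delivery.

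Leakage costs the change contrast, or a covariance-adjusted estimate that uses this baseline, less than 1.5 points, and nothing in the post-test comparison. The overlap lowers the year average below the fully delivered effect unless onset is immediate. At L = 0, power with 31 groups per arm lies between 38% (worst case) and 83%, and with 40 between 47% and 91%. A reader might take the low figures as the trial's actual power. The document does not support that, because it gives no onset shape and does not say whether 9 points is the year average or the completed-programme effect. That ambiguity is the defect in the planning figure.

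**What to change.** 1. End each group's baseline year on the day before its first outreach visit (for control groups, the first visit of the control programme), using encounter dates in the extract. The article's list of extract contents does not mention dates, but software that selects a 12-month period must use them, and it is still to be developed. It should reach back far enough to fill a whole year before the visit.
2. State that the primary estimand is the average effect over the first year from initiation, and keep the season-balanced 12-month window. In Sample size and statistics, say that 27% to 18% is that average; if it is not, restate the assumed effect or the power. Align the wording in Outcome measures.
3. Prespecify a secondary analysis restricted to the months after the workshop. Cut control groups at the corresponding calendar date in the same geographical stratum, and adjust both arms for the same calendar months of the baseline year.

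Cost: revised wording, one extra analysis, a check that dates are in the extract, and a planning power that may read less favourably. No change to the intervention or to recruitment.

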### Data handling

Software aimed at extracting predefined data sets will be developed for this trial. The software will be compatible with the four EPRs (Infodoc^®^, WinMed^®^, ProfDoc Vision^® ^or System X^®^) used by the large majority of Norwegian GPs. The dataset from each individual GP will provide information on number of patient appointments, and main diagnosis linked to each appointment with patients with a respiratory tract infection. Diagnosis will be based on the International Classification of Primary Care (ICPC-2) [76]. Extracted data will also contain drug prescription details, described in terms of The Anatomical, Therapeutic, Chemical (ATC) classification system with Defined Daily Doses (DDDs), in short: The ATC/DDD system [79].

In order to merge prescription data provided by NorPD with data from the EPR systems, the Civil Personal Registration (CPR) number for each patient will be extracted from the EPR. These are the unique identification numbers for Norwegian citizens, and will be deleted from the research database after the record linkage has been performed. The dataset from NorPD will provide data on drugs actually dispensed.

Extracted data from each EPR will be encrypted, stored on a diskette and mailed to the principal researcher. A flow-chart of the data collection is summarized in Figure 3.

### Outcome measures

Primary outcome measures will be changes in prescription patterns after the tailored educational intervention in terms of prescriptions for antibiotics in out-patients with RTIs. The intervention will include the option of "delayed prescriptions". Following the intervention, prescription data will be collected one year after the first (baseline) gathering of prescription data. Change in prescription patterns in the intervention group will be compared with the non-intervention control group, and with a sample of Norwegian GPs not included in the current trial. The latter data will be provided by the NorPD. Outcome measures are summarized in Table 2.

### Pilot study

The prescription data extraction procedures and the two peer group visits will be piloted in one peer CME group, before the main trial.

### Recruitment and randomization

Block-randomization of peer CME groups will be done within geographical strata, each comprised of one or more counties. The size of the blocks will vary according to the number of recruited groups within each stratum. An independent researcher not involved in the study will be responsible for the randomization. Based on this randomization, peer groups will be assigned to either the intervention group or to the control group.

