### Sample size and statistics

A prevalence of 27% of inappropriate prescriptions of antibiotics for RTIs in general practice settings were found in two previous studies; one from Norway [80] and one from The Netherlands [62]. In accordance with these findings [62,80], we anticipate a baseline prevalence of inappropriate prescription of antibiotics for RTIs of 27% in the present study.

Flottorp et al. [63] demonstrated a 3% reduction of inappropriate antibiotic prescription for sore throat in a tailored intervention in general practice settings. This intervention was not, however, based on peer CME groups. This was considerably less than the 12% reduction (absolute value) of antibiotic prescription rates for RTIs found by Welschen et al. [62], in a peer group intervention trial.

In the present study we will consider a reduction of inappropriate prescriptions for RTIs by one third to be clinically significant. Assuming that the prevalence of inappropriate prescriptions in the control group remains constant, this equals a reduction from a baseline level of 27% to a post-intervention level of 18% or less (9% absolute reduction; 33% relative reduction).

The sample size calculation needs to take into account and adjust for intra-cluster (peer group) correlation, since the data within peer groups cannot be considered independent. The intra-cluster correlation is assumed to be 0.085, based on data from previous studies [63,78]. Furthermore, we expect an average of 7 participating doctors per peer group (allowing for some withdrawal) and an average of 300 cases of RTIs per GP during the intervention period, amounting to a total of 2100 cases per cluster. The variance inflation factor [81], used to correct the sample size, was therefore 179.

Based on these figures and applying an 80% power level and a 5% statistical significance level, we estimate an intervention sample size requirement of 31 peer CME groups and a corresponding number of control groups.

We will carry out post-test comparisons between the intervention and control group using cluster-adjusted chi-square and *t*-tests. Analysis of covariance may be used to adjust for imbalance of baseline levels between the intervention- and control-groups [82]. The data set will primarily be analysed according to the cluster-randomization, however, analyses at physician- and sub-groups of physicians will also be performed, based on individual patients' data.

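### The peer groups are randomised within geographical strata, but the named comparisons carry no stratum term; if geography predicts prescribing, the test is conservative and some precision is lost

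*Protocol article*

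**What the plan says.** The article's section Recruitment and randomization sets a stratified scheme for allocating clusters: "Block-randomization of peer CME groups will be done within geographical strata, each comprised of one or more counties". Block size is not fixed: "The size of the blocks will vary according to the number of recruited groups within each stratum". The number of strata is not given.

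The section Sample size and statistics names the analysis: "We will carry out post-test comparisons between the intervention and control group using cluster-adjusted chi-square" and t-tests. One covariate method is mentioned, as an option and for one purpose: "Analysis of covariance may be used to adjust for imbalance of baseline levels between the intervention- and control-groups". The level of analysis is given as: "The data set will primarily be analysed according to the cluster-randomization". Strata appear in none of these sentences, nor in the sample-size calculation.

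**The concern.** Balanced allocation within strata puts nearly equal numbers of intervention and control groups in each region. Regional differences in prescribing then largely cancel out of the arm contrast, and its true sampling variance falls. A two-sample cluster-level test does not know this. It estimates the error from the whole spread of cluster results within each arm, including the spread between regions. The estimated standard error therefore exceeds the true one, intervals are wider than they need be, and the actual type I error lies below 5%.

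At stake is efficiency. The trial takes the trouble to stratify, and the named tests would not collect the precision that this buys.

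**Working it through.** **Inputs from the article (Sample size and statistics; Participants).** Rates 27% and 18%; "applying an 80% power level and a 5% statistical significance level"; intra-cluster correlation 0.085; 7 doctors × 300 cases = 2100 cases per cluster; variance inflation factor 179; 31 groups per arm; recruitment aim about 80 groups, or about 40 per arm.

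**Assumptions, not in the article.** Number of strata S (8, with 4 as a check). Share f of between-cluster variance lying between strata (0 to 20%). Two-sided testing, since sidedness is not stated.

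**1. Reproducing the stated sample size.** Variance inflation factor = 1 + (2100 − 1) × 0.085 = 179.4. Two proportions, 27% against 18%, two-sided 5%, 80% power, with continuity correction: 359 cases per arm before inflation. Then 359 × 179 / 2100 = 30.6, so 31 groups per arm, as stated. Without the continuity correction the result is 337 and 29 groups. One-sided versions give 23 to 25 and do not match. No stratum term enters, so adding one to the analysis leaves the 31 unchanged.

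**2. Standard error at 31 per arm.** Variance of a cluster proportion = [(0.27 × 0.73 + 0.18 × 0.82) / 2] × 179.4 / 2100 = 0.17235 × 0.0854 = 0.01472, so SD = 0.1213. SE of the difference = 0.1213 × √(2/31) = 0.0308. Almost all of this variance is between clusters (0.085 out of 0.0854), so f can be applied to the whole.

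**3. Closed-form approximation.** The true SE is 0.0308 × √(1 − f), while the unstratified test goes on using about 0.0308.
- SE inflation = 1/√(1 − f): 1.05 at f = 10%, 1.12 at 20%.
- Actual type I error = 2 × [1 − Φ(1.96/√(1 − f))]: 3.9% and 2.8%.

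This charges nothing for lost degrees of freedom and treats the between-stratum variance as fully realised, so it slightly overstates the effect.

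**4. Simulation at cluster level.** 20,000 runs per cell, near-equal strata, allocation balanced within strata, normal cluster results, total variance held at the value in step 2. An unstratified two-sample t-test is compared with the same test plus stratum terms, for a 9-point effect and S = 8. Read across each row: because total variance is held fixed, power in both columns rises with f.

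| Groups per arm | f | Power, no stratum | Power, with stratum | Type I, no stratum | Type I, with stratum |
|---|---|---|---|---|---|
| 31 | 0% | 0.818 | 0.814 | 0.053 | 0.052 |
| 31 | 5% | 0.824 | 0.834 | 0.048 | 0.053 |
| 31 | 10% | 0.832 | 0.855 | 0.040 | 0.049 |
| 31 | 20% | 0.850 | 0.892 | 0.031 | 0.050 |
| 40 | 20% | 0.931 | 0.955 | 0.031 | 0.049 |

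The simulation error of a type I figure is about √(0.05 × 0.95 / 20,000) = 0.0015, so the f = 0 values are compatible with 5%. At 31 per arm, the mean estimated SE of the unstratified test against the true SE is 0.0306 / 0.0293 = 1.04 at f = 10% and 0.0304 / 0.0275 = 1.11 at f = 20%. With the stratum in the model at f = 20%, the mean estimated SE is 0.0276, which matches the true 0.0275.

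**5. Sensitivity to the number of strata.** With S = 4 at 31 per arm, power is 0.836 against 0.855 at f = 10%, and 0.854 against 0.893 at 20%. The result hardly depends on S in this range.

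**The case against.** The strongest reply is that this is a condensed article. It never says that strata will be left out, and the choice of model terms is usually completed in an analysis plan. A cluster-adjusted test could be run in a stratified form. This carries some weight: if the full plan already includes the strata, only the article's wording is behind. But the article does name its tests and its one covariate adjustment. As named, they account for clustering and not for stratification, so a stated method can be improved here.

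Second, the loss depends on geography being prognostic, and nothing in the article establishes that. This stands in full. At a share of nil there is nothing to gain; at 5% the gain is one point of power.

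Third, stable regional differences would largely be removed by adjusting for baseline or by comparing change. The Outcome measures section speaks of comparing change, and covariance adjustment is allowed. This also stands as mitigation. It does not settle the point, because the adjustment is optional and the Methods/Design and Sample size and statistics sections describe comparisons at follow-up.

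A reader might also infer that the plan contradicts itself, because it says "The data set will primarily be analysed according to the cluster-randomization" while the tests omit the strata. The text does not support that. The same sentence goes on to announce further analyses at physician level, so the phrase sets the level of analysis, cluster as against physician. It promises nothing about strata.

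**Conclusion.** The point holds as a conditional loss of efficiency. If strata explain 10 to 20% of between-group variance, with 8 strata and 31 groups per arm, omitting them makes the standard error about 4 to 11% too large. It lowers type I error to about 0.04 to 0.03 and gives up about 2 to 4 points of power (0.855 − 0.832 = 0.023; 0.892 − 0.850 = 0.042). At 40 per arm and 20%, the loss is 0.955 − 0.931 = 0.024. All these figures are before any baseline adjustment, which would reduce them. Both the share and the number of strata are assumptions.

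Two stronger conclusions might be drawn and neither is supported. One is that the trial would be underpowered: the unstratified test keeps about 82% or more at 31 per arm in every scenario examined, and about 80 groups are sought. The other is that the result would be invalid: the error is in the conservative direction and does not raise the false-positive rate. This is a modest improvement that is worth making because it is nearly free.

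**What to change.** State in the analysis section that the primary cluster-level comparison includes the randomisation stratum, either as a fixed effect in the analysis of covariance or mixed model, or through a stratified cluster-level test. Any permutation test should re-randomise groups within strata. If a fuller plan already does this, bring the article's wording into line with it.

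The cost is one phrase of text and (number of strata − 1) degrees of freedom. With 8 assumed strata that is 7 out of 62 − 2 = 60 at 31 groups per arm, or 7 out of 80 − 2 = 78 at 40 per arm. If the strata prove uninformative, the price at 31 per arm is about 0.004 of power (0.818 against 0.814). The sample size does not change.
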